## Methods

### Data Collection

Data on health consequences will be collected by means of participant completed questionnaires collected at baseline and 12 months follow-up to capture changes in health-related quality of life outcomes (measured by EQ-5D-5L).

The associated costs will relate to resources required to provide the intervention and usage of NHS, public and personal social services as well as patient cost during the follow-up period. Within the pilot feasibility study we will compare different cost assessment tools. Questionnaires will be tested for their appropriateness to collect relevant information, which will be assessed by the amount of missing data. Open-format case diaries for staff will be used to inform on the type of activities and associated time required to deliver the interventions. These diaries will be used to produce tailored data collection tools for the definitive trial which are as parsimonious as possible.

### Data Analyses

The initial stage of value of information analysis will be the construction of a mathematical decision model that will synthesise the best available existing evidence from the literature and information from the pilot feasibility trial in order to provide preliminary estimates of effects, costs and cost-effectiveness. Uncertainty around estimates of effects, costs and cost-effectiveness will be accounted for by probabilistic sensitivity analysis and estimated using Monte Carlo simulation, as cost data are unlikely to be normally distributed. Statistical imprecision will be presented as confidence intervals around differences in effectiveness, costs and cost-effectiveness. Threshold sensitivity analyses will be applied to identify the range for costs and effects in which a treatment might need to exist in to be considered cost-effective with respect to standard thresholds for cost-effectiveness (e.g. £20,000 per QALY).

We anticipate that the results of the analysis described above will be insufficient to inform practice because of the amount of uncertainty that surrounds estimates. The VoI analysis will build upon the results of the probabilistic sensitivity analysis to estimate the expected value of sampling information (EVSI). The EVSI will quantify the value of reducing uncertainty via collection of additional data in a definitive trial. Comparing the value of additional information with the financial and opportunity cost to generate the additional information, the expected net gain (ENG) can be calculated as difference between the EVSI and total cost of conducting the further research. The optimal design of a definitive trial will maximise the expected net gain (ENG) to society with regard to sample size. The optimal sample size is that which maximises the difference between EVSI and expected total cost of the research (both the direct cost of the research itself and the opportunity cost of delaying the implementation of a worthwhile intervention whilst research is on-going). The estimated optimal sample size will be inflated according to the rate of missing data in the trial data to achieve the optimal sample size of complete data cases and to determine the final sample size for a definitive trial.

As with any method of estimating sample sizes there will be a number of uncertainties (e.g. the number of people who might benefit from one of the behavioural interventions over the expected time that the therapy might be used before becoming obsolete). For the VoI analysis we will explore these and estimate the impact on sample size estimates.

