| **Exclusion criteria** | - Actively receiving treatment from drug and alcohol services - Unable to access drug and alcohol services e.g. due to imminent move out of area. - Unable to give informed consent due to capacity or language barriers |
| **Outcome of pilot feasibility trial** | Stop/Go criteria have been developed for progression to a definitive trial.  Definite Go (‘green light’) defined as :   - ≥60% of eligible participants consenting to pilot feasibility trial; - ≥ 80% LAC attend ≥ 60% of sessions as planned in a given intervention arm. - Retention of ≥ 70% of consented participants for provision of key outcome data at 12 months. - The intervention can be delivered with fidelity i.e. the content, frequency, duration and quality of the intervention can be delivered as set out in the intervention delivery manual. - An indication from qualitative interview and focus group work that the intervention(s) is (are) perceived as acceptable to both young people and Drug and Alcohol workers.   Definite Stop (‘red light’) defined as :   - < 40% of eligible participants consenting to pilot feasibility trial - < 20% LAC attend ≥ 60% of sessions as planned in a given intervention arm. - retention of < 50% of consented participants for provision of key outcome data at 12 months - Value of information analysis shows that future research is not worthwhile (i.e. the expected value of sampling information (EVSI) < £0. - It is clear from the process data from staff and participants that the intervention procedures have low fidelity in terms of content, frequency, duration and quality and that they are unfeasible to deliver. - An indication from qualitative interview and focus group work that the intervention(s) is (are) not acceptable to LAC and Drug and alcohol workers |
| **Primary Outcomes in definitive trial** | - Episodes of heavy episodic drinking (≥5 units in 1 day) in the preceeding 30 day period - Frequency of use of the most problematic classified substance in preceeding 30 days   (data from Timeline Follow-back questionnaire-30) |

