## Objectives

Primary Objectives

Phase 1 Formative Study: To adapt two behaviour change interventions for Looked After Children (LAC) and care leavers to help reduce risky substance use: i, Motivational Enhancement Therapy (MET); ii. Social Behavioural Network Therapy (SBNT). This will be carried out with LAC and care leavers, their carers, drug and alcohol workers, and LAC social workers to ensure acceptability and feasibility of the intervention packages.

Phase 2 Pilot Feasibility RCT: To conduct a three arm pilot RCT (comparing: i. MET, ii. SBNT, and iii. Control – usual care), to determine if rates of eligibility, recruitment and retention of LAC, and acceptability of the interventions are sufficient to recommend a definitive multi-centre randomised controlled trial.

Secondary research objectives:

Phase 1 Formative Study:

1. To refine the intervention packages for integration into LAC care pathways.
2. To conduct an electronically administered survey with LAC service leads across England to characterise usual care locally and nationally, and identify potential collaborative centres for a future multi-centre RCT.

Phase 2 Pilot Feasibility RCT:

1. To establish response rates, variability of scores, data quality and acceptability of the proposed outcomes measures for self-reported alcohol and drug use, health related quality of life, mental health and well-being, sexual behaviour and placement stability 12 months post recruitment, in order to inform a sample size calculation for a definitive multicentre RCT.
2. To assess acceptability, engagement and participation with the MET and SBNT based interventions by LAC, their carers and front line drug and alcohol workers.
3. To carry out a process evaluation to include fidelity of intervention delivery and qualitative assessment of the barriers to successful implementation; and to assess if key components from the MET and SBNT interventions can be combined to develop a new optimised intervention.
4. To develop cost assessment tools, assess intervention delivery costs and carry out a value of information analysis to inform a definitive study.
5. To apply pre-specified ‘stop: go’ criteria and determine if a definitive multi-centre randomised controlled trial is feasible, and, if so, develop a full trial protocol.

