## Sample Size Calculation

The pilot feasibility trial will aim to obtain data from a minimum of 35 respondents in each trial arm at 12 month follow-up, to estimate the critical parameters to the necessary degree of precision with a continuous primary outcome, (number of occasions drinking 5+ standard drink units in a single occasion as derived from the TLFB/30).[^69^](#_ENREF_69) Assuming a pessimistic 30% loss to follow up, the sample size to be recruited will be inflated to 50 young people in each of the three arms.

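### Missing data enters the value-of-information sample size only after the optimum is found, so the final recruitment number may overshoot the plan's own net-gain criterion

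*Protocol*

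**What the plan says.** Protocol section 11.2.2 (Data Analyses) sets out two steps in order.

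1. The criterion: "The optimal sample size is that which maximises the difference between EVSI and expected total cost of the research". Cost is to cover "both the direct cost of the research itself and the opportunity cost of delaying the implementation of a worthwhile intervention".
2. The adjustment: "The estimated optimal sample size will be inflated according to the rate of missing data in the trial data", the purpose being "to achieve the optimal sample size of complete data cases and to determine the final sample size for a definitive trial".

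Missing data appears only in step 2. The section does not say whether cost in step 1 is counted per person recruited or per complete case. Nor does it say that ENG is recomputed or maximised again at the inflated size. Its closing paragraph promises to explore uncertainties that bear on the sample size. The example given is the number of people who might benefit; attrition is not named.

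The missing-data rate is to come from the pilot. The protocol's own planning figure is in section 10.3: "Assuming a pessimistic 30% loss to follow up". In the Trial Summary one Go criterion is "Retention of ≥ 70% of consented participants for provision of key outcome data at 12 months", and the matching Stop criterion is retention below 50%.

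**The concern.** Dividing a target by (1−m) is the right adjustment when the number of complete cases is fixed in advance, for example by a precision or power requirement. Here the target is not fixed in advance. It is the point where one more complete case is worth no more than it costs, so it depends on the price of a complete case. Attrition raises that price, because several recruits may have to be paid for to obtain one complete record, and the optimum in complete cases then falls. If the optimum is found at the lower price and inflated afterwards, the final number carries a target that the plan's own criterion would not choose.

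Two things would be at stake. The definitive trial could be advised to recruit more looked-after young people than the ENG criterion supports. And any net gain quoted at the uninflated size would leave out the cost of the added recruits.

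**Working it through.** **The pilot figure, for reference.** Section 10.3 aims for "a minimum of 35 respondents in each trial arm at 12 month follow-up". With 30% loss, 35/(1 − 0.30) = 50 per arm, and 3 × 50 = 150. This reproduces exactly and is not in question: 35 is a precision target, so inflating it is correct. The protocol states no value-of-information sample size, so there is none to reproduce.

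**Algebra.** Let n be complete cases, N recruits, m the missing rate, so n = N(1−m), and c the marginal cost of a recruit, including delay.

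- If step 1 uses one n for both terms, it solves EVSI′(n) = c.
- If lost recruits cost as much as completers, a complete case costs c/(1−m), and the ENG maximum solves EVSI′(n) = c/(1−m). At m = 30% that price is 1/0.7 = 1.43 times c.
- With diminishing returns, the first solution is the larger. Dividing it by (1−m) carries the excess into N.

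**Large-sample limit.** Put EVSI = EVPI − a/n (EVPI being the expected value of perfect information), so EVSI′ = a/n².

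- Step 1 gives n* = √(a/c), and the inflated size is n*/(1−m).
- The ENG maximum is at n = n*√(1−m), that is N = n*/√(1−m).
- Ratio of the two recruitment numbers: 1/√(1−m).

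| m | 1/√(1−m) | Excess recruitment |
|---|---|---|
| 20% | 1.118 | 12% |
| 30% | 1.195 | 20% |
| 50% | 1.414 | 41% |

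If a lost recruit costs a fraction f of a completer, the ratio is √(1 + f·m/(1−m)). At m = 30% and f = 0.7 this is √1.3 = 1.14. At f = 0 it is 1, and there is no excess.

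**Finite-sample illustration. All inputs are assumptions, because the protocol gives none.** Two arms; prior mean of incremental net benefit £0 and prior SD σ₀ = £600; individual SD σ = £6,000; 10,000 beneficiaries; fixed cost £0.5m; £1,000 per recruit; m = 30%. With n complete cases per arm, EVSI(n) = 10,000 × 0.3989 × σ₀²/√(σ₀² + 2σ²/n).

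- Optimise without attrition, then inflate: n = 209 per arm, N = 2 × 209/0.7 = 597, ENG £613,947.
- Optimise over recruits: n = 156 per arm, N = 2 × 156/0.7 = 446, ENG £638,809.
- Excess recruitment 209/156 − 1 = 34%. ENG lost £638,809 − £613,947 = £24,862, about 1.6% of EVSI.
- If cost is already taken as c/(1−m) per complete case, optimising and then inflating gives 446, against 445 from direct optimisation over recruits. That is a rounding difference.

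**Range.** The assumptions were varied: prior mean £0 or −£300, £1,000 or £3,000 per recruit, 2,000 to 50,000 beneficiaries, with and without removing recruits from the beneficiaries. Keeping scenarios whose best ENG is positive:

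| m | Excess recruitment | ENG lost, as % of EVSI |
|---|---|---|
| 20% | 15-29% | 0.2-1.2% |
| 30% | 25-52% | 0.6-3.5% |
| 50% | 55-138% | 2.7-18% |

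**Net gain quoted at the uninflated size.** The recruits left out number n*/(1−m) − n*. At m = 30% that is 0.43n*, so 43% of the per-recruit cost used in step 1 would be missing.

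**The case against.** The strongest reply is that the text never says attrition is ignored in step 1. It describes the optimum as a number of complete cases and the cost as an expected total. Both phrases fit a cost function that already pays for recruits who are lost, and on that reading inflating afterwards is exact. This stands, and it makes the finding conditional. A reader might infer that the optimisation assumes nobody is lost and that the final size must therefore be off the maximum; the document does not support so firm a claim. It does leave the unit of cost unstated, and with one n for both terms the natural reading gives the overshoot.

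A second reply is that the harm is small by the plan's own measure, because ENG is fairly flat near its maximum. That also stands at 20-30% loss. The larger losses arise around 50%, the edge of the pilot's own Stop region, and the 30% is a planning figure described as pessimistic; the plan will use the rate observed.

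A reader might also infer that the pilot's progression decision is biased. The documents do not support this: the value-of-information Stop criterion is written on EVSI below zero, not on ENG, and section 11.1 presents the analysis as additional evidence for funding and an aid to design. The promised sensitivity work could cover attrition, but the section does not commit to it.

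**Conclusion.** The point holds in conditional form, with moderate confidence. Section 11.2.2 fixes an order, optimise and then inflate, without saying that lost recruits are priced in or that ENG is re-evaluated. If EVSI and cost share the uninflated n and lost recruits cost as much as completers, the final size is too large by 1/√(1−m) in the large-sample limit, about 20% at 30% loss. Any ENG quoted at the uninflated n then omits the cost of the added recruits. If lost recruits are already priced, or cost nothing, there is no error.

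The direction follows from the stated criterion on that reading. The closed-form percentages also need the large-sample form of EVSI. The finite-sample sizes and ENG losses rest wholly on assumed inputs, a two-arm comparison and no separate cost of delay, and are illustrations only. What is affected is mainly the recommended recruitment number for the definitive trial; no pilot estimate or stop/go rate changes.

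**What to change.** Replace the inflation sentence in section 11.2.2 with wording such as: *ENG will be maximised over the number recruited N, with EVSI evaluated at N(1−m) complete cases and direct and delay costs evaluated at N; m is taken from the pilot and varied in sensitivity analysis.* Report ENG at that N.

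This is right on either reading: it reproduces the planned answer if attrition is already priced and corrects it if not. The cost is one sentence and one extra term in the code, with no new data. The recommended size and the stated net gain may both come out smaller.

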# DATA HANDLING

## Data Collection Tools and Source Document Identification

Baseline data will be collected after informed consent and will record demographics, placement type, drug and alcohol usage (AUDIT/Alcohol, Smoking and Substance Involvement Screening Tool (ASSIST) [^52^](#_ENREF_52)), mental health and well-being (baseline SDQ and WEMWBS) and health-related quality of life (EQ-5D-5L). These data will be collected electronically on tablet computers and transferred to the university server.

Follow up questionnaires will comprise:

- The 7 and 30 day Timeline Follow-back (TLFB).[^70^](#_ENREF_70) The TLFB-30 (and 7 day) will be compared to the shorter AUDIT, ASSIST and CRAFFT tools[^39^](#_ENREF_39)
- Mental health and wellbeing measured using the Strength and Difficulties Questionnaire (SDQ) and the Warwick-Edinburgh Mental Well-being scale (WEMWBS). [^40^](#_ENREF_40)^,^ [^41^](#_ENREF_41)
- Health related quality of life measured using the EQ-5D-5L.[^42^](#_ENREF_42)
- Self-reported occasions of ‘drunkenness’ in the last 30 days (past 30-day intoxication in ESPAD[^7^](#_ENREF_7)) to compare against the objective standard-drink unit measure.
- Placement stability for the young person – as part of the 12 month follow up questionnaire, questions will be developed and administered around placement stability. In addition consent will be obtained to link to social services records to assess longer term placement stability.
- Sexual behaviours measured using items taken from the computer assisted self-interview (CASI) questionnaire used in the Avon Longitudinal Study of Parents and Children (ALSPAC) supplemented with questions relating to regret in sexual encounters and unprotected sex used in the ESPAD.[^7^](#_ENREF_7)^,^ [^43^](#_ENREF_43)
- A questionnaire on antisocial and criminal behaviour used in ALSPAC. [^44^](#_ENREF_44)
- A bespoke questionnaire on use of health and personal social services.

All questionnaires will be developed during the formative research phase. The baseline and follow up questionnaires will be considered source data. Qualitative, economic and process data will also be considered as source.

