## Primary Outcome for Future Trial

Our study ultimately aims to decrease both alcohol and drug use in LAC; as such the proposed primary outcomes of the definitive trial, to be rehearsed in the pilot feasibility trial, will be heavy episodic drinking and frequency of use of the most problematic classified substance. Heavy episodic drinking (high intensity ‘binge’ drinking) in the preceding 30 day period will be derived from Timeline Follow Back data covering the last 30 days (TLFB-30) [^37^](#_ENREF_37) and defined as the 'number of occasions where 5 or more standard drink units are consumed on a single drinking day' as used in the ESPAD survey.[^7^](#_ENREF_7) This measure has been chosen as an objective measure of likely intoxication or ‘drunkenness’ which in turn is associated with behavioural risk taking. The most problematic classified substance (excluding alcohol) will be defined using the multi-criteria decision analysis hierarchy developed by Nutt et al.[^38^](#_ENREF_38); we will again use data from TLFB-30. While the most prevalent drugs for the general population of under 18 year olds are alcohol and cannabis, NPS use is becoming increasingly common.[^9^](#_ENREF_9) NPS will be classified along with mephedrone. The TLFB-30 will be compared to first 7 days of TLFB and the shorter AUDIT, ASSIST and CRAFFT tools[^39^](#_ENREF_39) in terms of data yield, pilot feasibility and acceptability as part of planning for the future multi-centre RCT. This group of young people that have often had to fill out paper work in terms of their LAC status and findings from our PPI work have highlighted the importance of respondent fatigue. Longer instruments may lead to respondent burden and incomplete data. The study needs to assess the accuracy but also the efficiency of the tools we use. As such data yield from the TLFB -7, and the shorter AUDIT, ASSIST and CRAFFT will be compared to the TLFB-30.

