# TRIAL PROCEDURES

A three arm pilot feasibility randomised controlled trial will be conducted in three sites in the North East of England: Newcastle, Durham and Teesside, to assess the acceptability of the adapted interventions (SBNT and MET) and the feasibility of taking one or both of the interventions to a full scale multicentre randomised controlled trial. Details of the flow of participants through the study is presented in Figure 2.

Figure 2 Component parts of the SOLID study phase 2

North East Fuse Network: Newcastle, Gateshead, Durham, Middlesbrough, Stockton and Redcar.

**Social worker** screening of all LAC 12-20 years for significant drug/ alcohol use and meeting inclusion criteria (LAC ages 12-20 years, admitted substance use in past 12 months and consents to take part in the study).

Request for assent to contact research team.

[Young people initial contact, assent and CRAFFT- Doc 16]

**Consent/assent not given**- LAC not enrolled into study continues with usual care

**Assent given and inclusion criteria met-** Participant information sheet sent out to YP and parent/guardian.

[Participant information leaflet YP 12-14 or YP 15-20- Doc 17 or 18: sent out by SOLID Admin lead]

Usual care + signposting - services

Drug and alcohol service delivered

Motivational Enhancement Therapy

Drug and alcohol service delivered

Social Behavioural Network Therapy

S

**Researcher Visit 2. Follow-up Evaluation** 12 months post enrolment:

*Substance use (TLFB substance use/30 day, AUDIT and ASSIST)

*Mental health and wellbeing (SDQ, WEMWBS) *Quality of life (EQ-5D) * Sexual behaviour (CASI & ESPAD questions) *antisocial and criminal behaviour *placement stability and *use of health and social services.

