**Researcher visit 1**

**Consent/Assent given**

**Baseline data collection**. LAC to complete electronic data collection form.

Baseline data collection including *demographics, *placement type, *drug and alcohol use (AUDIT/ASSIST), *mental health and well-being (baseline SDQ and WEMWBS) * Self-reported drunkenness and *health-related quality of life (EQ-5D-5L).

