### Screening

LAC within the service are already questioned regarding their drug and alcohol use as part of routine care, however, the tools used are not standardised. Services in the area have agreed to screen all LAC aged 12-20 years for drug and alcohol use by a social worker using the validated 6 question CRAFFT and for anonymised data to be processed in Newcastle. This will ensure that data is accurately recorded and summary statistics can be fed back to each local authority. The CRAFFT has been used extensively with young people, and is sensitive and specific to identify problem substance use.[^39^](#_ENREF_39) Information leaflets introducing the study will be shared with the young person by the social worker. As part of clinical care, anonymised information will be processed centrally; this will include age, gender and locality. Written assent will be obtained from all LAC aged 12-20 for the young person and their parent/ guardian to be contacted by the research team depending on the CRAFFT score. Those scoring ≥2 in the CRAFFT (‘at risk of substance misuse’) will be contacted by the research team if written assent for contact has previously been given to the social worker. Young people that are in active treatment with drug and alcohol services will not be screened as they will not meet eligibility criteria. A screening log will be kept by the social worker to ensure all LAC aged 12 to 20 years who are not in active treatment with drug and alcohol services have the opportunity to be enrolled into the study.

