## Follow-up Assessments

All young people enrolled into the trial study will be contacted by phone and letter/email 12 months post recruitment to complete a follow up electronic questionnaire. A recruitment window of 8 weeks will be in place to maximise follow up.

The questionnaire will be administered by the study research associate who will visit the young person in their home/ convenient location. If after repeated attempts the researcher is not able to contact the young person for a face to face follow up, a telephone follow up will be offered. As in the baseline questionnaire, data will be collected using electronic data capture forms programmed onto digital tablets. The researcher will hand the LAC the tablet and be present to answer questions as necessary. The Time line Follow back will be researcher administered.

The data to be collected are listed in Section 3.4 and 3.5. In summary these data are:

- Time Line Follow Back 30 day:
  - Episodes of heavy episodic drinking (≥5 units in 1 day) in the preceeding 30 day period
  - Frequency of use of the most problematic classified substance in preceeding 30 days
- AUDIT and ASSIST
- Mental health and wellbeing: Strength and Difficulties Questionnaire (SDQ) and the Warwick-Edinburgh Mental Well-being scale (WEMWBS).
- Quality of life measured using the EQ-5D-5L.
- Placement stability for the young person
- Sexual behaviour: taken from ALSPAC the computer assisted self-interview (CASI) with questions relating to regret in sexual encounters and unprotected sex used in the ESPAD.
- Antisocial behaviour questionnaire previously used in ALSPAC.
- Use of health and social services using a bespoke questionnaire

In addition, process evaluation data will be collected as presented in Section 7.

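### CRAFFT is named as a comparator for TLFB-30, but the two are never given at the same visit, so no concurrent comparison is possible for that tool

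*Protocol*

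**What the plan says.** Section 3.4 (Primary Outcome for Future Trial) states that "the shorter AUDIT, ASSIST and CRAFFT will be compared to the TLFB-30". It frames the exercise "in terms of data yield, pilot feasibility and acceptability as part of planning for the future multi-centre RCT" and adds: "The study needs to assess the accuracy but also the efficiency of the tools we use". The reason given is respondent fatigue: a long instrument may burden this group and leave incomplete data. Section 12.1 repeats the plan in its list of follow-up questionnaires: "The TLFB-30 (and 7 day) will be compared to the shorter AUDIT, ASSIST and CRAFFT tools".

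The places that fix what is collected, and when, read differently:

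- Table 1 (section 5.7.1) marks CRAFFT in the screening column only and TLFB-30 in the 12-month column only. AUDIT and ASSIST are marked at baseline and at 12 months.
- The follow-up box of Figure 2 lists "Substance use (TLFB substance use/30 day, AUDIT and ASSIST", without CRAFFT.
- The summary list in section 5.5 has "AUDIT and ASSIST" beside the Timeline Follow-Back, without CRAFFT.
- Section 5.2.2 has screening done "by a social worker using the validated 6 question CRAFFT", and section 5.1.1 requires a score of 2 or more for entry.

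On a second item, the baseline box of Figure 2 includes "Self-reported drunkenness and *health-related quality of life (EQ-5D-5L", but its follow-up box has no drunkenness item. Table 1 marks drunkenness at 12 months only.

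**The concern.** One use of this pilot is to learn whether a shorter tool could stand in for TLFB-30. Section 3.2 makes data quality and acceptability of the outcome measures an objective of the pilot trial, and section 10.2.2 uses the results to inform the choice of instruments for the definitive trial. Judging one tool against another needs both from the same person at about the same time. If the tablet questionnaire is built from Table 1, that pairing will not exist for CRAFFT and cannot be recreated once the 12-month visits are over. An analysis plan cannot repair this, because the visit at which an instrument is given is fixed by the protocol.

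**Working it through.** **Step 1. Instruments by time point (Table 1).**

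| Instrument | Screening | Baseline | 12 months | Shares a visit with TLFB-30 |
|---|---|---|---|---|
| TLFB-30 | no | no | yes | – |
| AUDIT | no | yes | yes | yes |
| ASSIST | no | yes | yes | yes |
| CRAFFT | yes | no | no | no |

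The 7-day Timeline has no row of its own. Section 3.4 takes it from the first 7 days of the Timeline, so it is available whenever TLFB-30 is.

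**Step 2. The gap.** Table 1 times follow-up from baseline, the trial summary allows an 8-week window after 12 months, and screening comes before baseline. The minimum gap is 12 months. With the full window it is 12 + 56/30.4 = 12 + 1.8 = about 13.8 months, plus the interval from screening to baseline, which the protocol does not state. All intervention sessions fall inside this gap.

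**Step 3. How many pairs.** Section 10.3 plans 35 respondents per arm after 30% loss: 35/(1 − 0.30) = 50 recruited per arm, and 3 × 50 = 150, which matches the trial summary. Respondents at 12 months: 3 × 35 = 105. Same-visit pairs with TLFB-30 are then up to 105 for AUDIT, up to 105 for ASSIST, and 0 for CRAFFT.

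**Step 4. Could the screening CRAFFT serve instead?** Take each purpose in section 3.4 in turn.

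- Data yield: every randomised participant must have a CRAFFT score to enter, so completion is 150/150 = 100% by design. TLFB-30 can reach at most 105/150 = 70% at the planned retention. The 30-point difference would appear even if the two tools were equally easy to complete, because it reflects attrition and the entry rule.
- Feasibility and acceptability: CRAFFT is given by a social worker before enrolment, and TLFB by a researcher at follow-up (section 5.5). Any difference mixes the tool with who administers it, where and when.
- Accuracy: the two scores describe different periods at least 12 months apart, and 2 of 3 arms (100 of 150 participants) are offered an intervention in between that is meant to change the quantity measured.

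**Step 5. Self-reported drunkenness, side by side.**

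| Place | Baseline | Follow-up |
|---|---|---|
| Figure 2 | listed | not listed |
| Table 1 | not marked | marked |
| Section 12.1 | not listed | listed |
| Section 5.3 | not listed | (baseline section only) |

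Section 5.5 leaves the item out of its summary list but refers to section 3.5, which includes it. Figure 2 is the outlier in both columns.

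**The case against.** The strongest reply is that section 12.1 puts the CRAFFT sentence inside the list of follow-up questionnaires, and that section 5.5 points back to section 3.4, where CRAFFT is named. On that reading CRAFFT is meant to be given at 12 months and Table 1 merely leaves it out. This is plausible, but it means that Table 1, the summary list in 5.5 and Figure 2 are incomplete, so the amendment is needed either way.

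A second reply is that section 3.4 speaks mainly of yield, feasibility and acceptability, which can be described without same-day measurement. This stands in part: a crude description from two occasions is possible, so it would be wrong to say that no comparison of any kind can be made. But accuracy is also named, and Step 4 shows that the yield comparison would be settled by the design.

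A reader might go further and infer that only CRAFFT scores of 2 or more exist, so that specificity cannot be estimated. The protocol does not support that. Section 5.2.2 has all eligible-age young people not in active treatment screened, and anonymised data held centrally, so screen-negative scores do exist; what they lack is a TLFB-30. Adding CRAFFT at 12 months would not undo the selection at entry, and the protocol names no TLFB-30 threshold against which specificity would be defined.

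A reader might also infer that the missing baseline drunkenness value raises the definitive trial's sample size, through a lost covariate adjustment. That does not follow. Drunkenness is a secondary outcome, the pilot is sized on heavy-drinking occasions from TLFB-30, a drunkenness correlation would not supply the TLFB-30 one, and AUDIT and ASSIST are already collected at baseline.

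**Conclusion.** The point holds for CRAFFT alone. As scheduled, it shares no visit with TLFB-30, and a concurrent comparison stated in two sections cannot be carried out: no same-visit pairs, against up to 105 for AUDIT and for ASSIST. The count assumes the protocol's own 30% loss and full completion among those followed up; the zero does not depend on either.

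It is a moderate point. The pilot's primary outcomes are recruitment, retention, acceptability and engagement, no stop/go criterion uses this comparison, and the other shorter tools can still be assessed as planned. It is nevertheless worth correcting before the first 12-month visit, since the data cannot be recovered later.

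The drunkenness discrepancy is secondary. Because Figure 2 has the item at baseline and not at follow-up, the reverse of Table 1, it may simply sit in the wrong box. The documents do not show that a baseline measurement was intended and then lost. Its stated use, a check against the drink-unit measure, works at 12 months as scheduled.

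**What to change.** Preferred: add the 6-item CRAFFT to the 12-month assessment in Table 1, section 5.5, section 12.1 and the follow-up box of Figure 2, and state how it is to be administered there (for example on the tablet, as for the other self-completed tools). The cost is six more short questions at an existing visit, for a group in which the protocol already worries about fatigue, and a small amendment before 12-month follow-up begins.

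If that burden is not acceptable, remove CRAFFT from the planned comparison in sections 3.4 and 12.1 and keep it as the screening tool. This costs only an edit, but gives up the evaluation of one candidate short instrument.

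In the same amendment, state once when self-reported drunkenness is collected and align Figure 2 (both boxes), Table 1 and sections 5.3, 5.5 and 12.1. If the 12-month timing is the intended one, this is an edit with no added burden; if baseline is also intended, it adds one item there.
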